#### **5.5 Data to be collected and when the data will be collected**

For both groups we will administer a survey to patients on admission, at discharge, and 30-days post-discharge. For both groups, we will administer a survey to caregivers at admission and 30-days post-discharge.

For the intervention arm only, within 30-days of discharge we will conduct qualitative interviews with the patient and their caregiver (if their caregiver consented to participate in the study, caregiver participation is not required for patient enrollment in this study) (please see more details below).

For the intervention arm, we will ask the rural home hospital MD to complete the MD AM Report each morning and the RHH RN/EMT-P to complete the Nursing visit form after each patient visit. Twice a week we will send the RHH clinicians the Clinician process measures survey. Post-discharge we will conduct qualitative interviews with rural home hospital clinicians only (please see more details below).

For both groups:

Clinical and administrative data will be extracted from electronic sources (e.g., enterprise data warehouse, electronic health record (EHR) at study sites). Cost data for the hospitalization and post-discharge period will be obtained from study site financial personnel using direct cost accounting methods. We will also collect information from patients and caregivers using IRB approved surveys and standardized questionnaires (see below). All data will be collected by trained study staff and inputted on a Partners encrypted shared drive. Data collected from filed research collection (including patient surveys) will be stored in REDCap (Research Electronic Data Capture, Vanderbilt University, Nashville, TN), which is fully HIPAA-compliant secure web application.

- All data collected at Alberta Health Services (Wetaskiwin Hospital) will also be stored on MGB REDCap

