#### 5.5.2 Secondary endpoints

| Measure                                                                                                       | Source                     | Day(s) Obtained         |
|---------------------------------------------------------------------------------------------------------------|----------------------------|-------------------------|
| Total cost, discharge to 30-days post discharge (published as percent change given sensitivity of these data) | Hospital accounting system | 30 days after discharge |
| Unplanned readmission within 30-days of discharge, %                                                          | EHR and patient report     | 30 days after discharge |
| Days at home (the number of days spent at home from the day of discharge to 30-days later)                    | EHR and patient report     | 30 days after discharge |
| Percent of day lying down                                                                                     | Biometric monitor          | Each day of             |

|  |  |           |
|--|--|-----------|
|  |  | admission |
|--|--|-----------|

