## **6.0 BIOSTATISTICAL ANALYSIS**

### **6.1 Quantitative**

We will present descriptive data with counts and percentages, means and 95% CIs, or medians and interquartile ranges, as appropriate.

The primary outcome (hospitalization cost) will be analyzed between arms, adjusted for site as a fixed effect, which accounts for difference across the three sites. . However, we will present cost data as the percentage of change in mean costs from control (rather than absolute difference) because of the sensitive nature of these data. The primary outcome will be assessed using a generalized linear model assuming a gamma distribution with a log link, given the skewed nature of cost, with treatment arm (control arm as the reference group) and site as fixed effects. The exponential of the treatment effect in this gamma regression model exactly equals the effect of interest (the percentage change from control). Patient characteristics should balance out across the two arms due to randomization, but if not, in the gamma regression, we will adjust for any of the follow patient characteristics that differ across arms: sex, age (continuous), education, and comorbid condition count (continuous). We *a priori* plan to also adjust for COVID case burden at each hospital only if COVID impacted home hospital operations. If the degree of rurality was different between patients at different sites, we *a priori* plan to adjust for degree of rurality.

We will use this same multivariable regression approach for secondary outcomes, using logistic regression for binary outcomes (e.g., readmissions) and negative binomial regression for count outcomes such as days at home, and non-transformed linear regression for normally distributed continuous outcomes (e.g., days at home), as appropriate. Given the multiple comparisons, we will use the Benjamini-Hochberg method for multiple comparisons for the secondary outcomes, with 0.2 as a prespecified false discovery rate.

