We *a priori* plan to perform a subgroup analysis that does not involve any extreme outlier participants (upper quartile plus 3 times the interquartile range) in either study arm, should this occur. We also *a priori* plan subgroup analyses by diagnosis, by age group, and by daily activity level. We may choose to employ non-parametric tests of significance should our data be nonparametric. We *a priori* plan to perform a subgroup analysis between continuous monitoring and intermittent monitoring sites. We *a priori* plan to perform a subgroup analysis by admission source (“from ED” vs “from ward” vs “from home”). We also plan to perform a secondary a priori subgroup analysis of US vs Canada.

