Secondary outcomes require slightly larger samples sizes at 80% power (with Type 1 error of 1%, approximately the type 1 error when using the Benjamini-Hochberg method as noted above). For Cost, discharge to 30-days, using a gamma regression model similar to total costs, with 66 patients in each arm, we have 80% to see an expected 65% reduction in the mean for intervention to control (we assume the over-dispersion parameter for the gamma distribution variance is 2.8 as seen from our preliminary data). For number of hours per day laying down (equivalently, % of day Lying down), using a negative binomial regression model with a logistic link with treatment and site effects, with 66 patients in each arm, we have over 90% to see an expected 65% reduction in the number of hours lying down for intervention to control (we assume the over-dispersion parameter for the negative binomial distribution is 1.4 as seen from our preliminary data). For percent with 30-day readmission, using logistic regression model with treatment and site effects, with 66 patients in each arm, we have 80% to detect on odds ratio of 0.25 for intervention on control (assuming the percent 30 day readmission in controls is 23% as seen in preliminary data). For the number of days at home, using a log-normal distribution with treatment and site effects, with 66 patients in each arm, we have over 80% to see an expected 65% increase in the number days at home for control to intervention (from 29 days to 48, days assuming the over-dispersion parameter for the negative binomial distribution is 1.4).

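### Post-discharge cost can be zero, but the protocol names a gamma model for it, does not say how zeros are handled, and does not say whether its dispersion of 2.8 included them

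*Protocol*

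**What the plan says.** Section 5.5.2 lists the endpoint as "Total cost, discharge to 30-days post discharge", to be reported as a percent change, with one source: "Hospital accounting system". Section 5.5 adds: "Cost data for the hospitalization and post-discharge period will be obtained from study site financial personnel using direct cost accounting methods".

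Section 6.1 gives the primary cost outcome a "generalized linear model assuming a gamma distribution with a log link, given the skewed nature of cost", and says the exponentiated treatment coefficient is the quantity of interest. It then extends the method: "We will use this same multivariable regression approach for secondary outcomes". The Power analysis names the model for this endpoint: "For Cost, discharge to 30-days, using a gamma regression model similar to total costs, with 66 patients in each arm". It claims 80% power for a 65% reduction, with a type I error of 1% and a gamma dispersion of 2.8 from preliminary data. The same paragraph assumes 23% readmission in controls and a detectable odds ratio of 0.25.

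The protocol does not mention zero costs. It does not say they are excluded, and it does not say they are kept. Its only flexibility is a general qualifier that the secondary models will suit the outcome, and this sentence in section 6.1: "We may choose to employ non-parametric tests of significance should our data be nonparametric".

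**The concern.** The reason given for the gamma model is skewness. That suits the index hospitalization, where every admitted patient has a positive cost. It does not carry over to the 30 days after discharge. On the protocol's own figure, 77% of controls are not readmitted, and those with no other recorded hospital contact would enter at zero. A gamma distribution gives zero no probability.

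If zeros are left out, the comparison is among users of care, a group defined by something the intervention is meant to change (readmission is part of the secondary aims in section 2.2). Patients who cost nothing after discharge are the best outcomes on this endpoint, so losing them can hide a saving made by avoiding readmissions. The number analysed would also fall below the 66 per arm behind the power statement.

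**Working it through.** **1. The stated power.** Inputs from the Power analysis: 66 per arm, ratio of means 0.35, dispersion 2.8, type I error 1%. Sidedness is not stated for secondary outcomes; two-sided is assumed, as for the primary.

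- SE of the log ratio = √(2 × 2.8 / 66) = 0.291
- |ln 0.35| = 1.050, and 1.050 / 0.291 = 3.604
- Power = Φ(3.604 − 2.576) = Φ(1.028) = 84.8% (83.7% with a t reference)

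The stated 80% is therefore somewhat conservative, provided 2.8 describes all patients. A 10% loss would give 80.0%, but no loss is stated.

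**2. What dropping zeros does to the ratio.** Let P be the share of an arm with positive cost. The arm mean is P times the mean among positives, so

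ratio among positives = ratio over all patients × (P control / P intervention).

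The size and direction of the distortion depend only on the two positive shares.

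**3. The bound from the protocol's figures.** The control odds are 0.23 / 0.77 = 0.2987. Multiplying by 0.25 gives 0.0747, so intervention readmission is 0.0747 / 1.0747 = 6.95%. Assume that only readmission generates cost, at equal mean cost in both arms.

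- All patients: 0.0695 / 0.23 = 0.302, a 70% saving
- Positives only: 0.302 × (0.23 / 0.0695) = 1.00, from 66 × 0.23 = 15.2 against 66 × 0.0695 = 4.6 patients
- If the all-patient ratio is instead the planned 0.35: 0.35 × (0.23 / 0.0695) = 1.16

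A simulation of 2,000 trials at this bound (squared coefficient of variation of cost per readmission assumed to be 1) gave median ratios of 0.28 with zeros kept and 0.95 with zeros dropped.

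**4. Range.** Assume that a share q of non-readmitted patients has a small cost, 5% of a readmission. For q = 25%:

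- Control mean: 0.23 + 0.77 × 0.25 × 0.05 = 0.2396; intervention mean: 0.0695 + 0.9305 × 0.25 × 0.05 = 0.0811; ratio 0.34
- Positive shares: 0.4225 and 0.3021; ratio among positives 0.3385 × 0.4225 / 0.3021 = 0.47

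| q | All patients | Positives only | Positive patients, control v intervention |
|---|---|---|---|
| 0% | 0.30 | 1.00 | 15.2 v 4.6 |
| 25% | 0.34 | 0.47 | 27.9 v 19.9 |
| 50% | 0.37 | 0.43 | 40.6 v 35.3 |
| 75% | 0.40 | 0.42 | 53.3 v 50.6 |
| 100% | 0.43 | 0.43 | 66 v 66 |

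With the small cost at 10% of a readmission, the pairs for 25%, 50% and 75% are 0.37 v 0.52, 0.43 v 0.50 and 0.48 v 0.51.

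**5. What software does with zeros.** The test data had 15 of 66 controls and 5 of 66 intervention patients at one equal positive cost and the rest at zero. R's glm with the Gamma family stopped with an error. A quasi-likelihood fit in R (log link, variance proportional to the squared mean) ran and returned 0.333, the ratio of arm means (5/15). The statsmodels gamma model with log link returned the same 0.333, with an infinite log-likelihood.

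**6. What 2.8 may mean for power.** If a share P is positive and the squared coefficient of variation among positives is v, then over all patients it is (1 + v)/P − 1.

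- *If 2.8 included zeros:* 1/P − 1 cannot exceed 2.8, so P is at least 1/3.8 = 26%. Power is the 85% of step 1.
- *If 2.8 came from positive costs only, with 80% of controls and 70% of intervention patients positive (assumed):* 3.8/0.8 − 1 = 3.75 and 3.8/0.7 − 1 = 4.43. SE = √((3.75 + 4.43)/66) = 0.352. Power = Φ(1.050/0.352 − 2.576) = 66%.
- *The same with 60% and 50% positive (assumed):* 5.33 and 6.60, SE = 0.425, power 46%.

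**The case against.** A reader might infer that the plan discards zero-cost patients and that a real saving will therefore vanish. The documents do not support this. No section excludes them, and the power statement counts 66 in each arm. The specified mean model, fitted by quasi-likelihood, keeps zeros and still estimates the ratio of means. Dropping is a risk that depends on software and analyst, not a stated plan.

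The share of zeros is also unknown. Section 5.5.3 tracks imaging, laboratory orders, clinician sessions, emergency visits and observation stays to 30 days. If these are costed, exact zeros may be few and the distortion small. The readmission-only case is a bound, not a forecast. It requires a squared coefficient of variation of at least 0.77/0.23 = 3.35 in controls and 13.4 in the intervention arm, which is impossible if 2.8 was computed over all patients. Nor does the bias always run toward no effect. By the formula in step 2 it disappears with equal zero shares and reverses if the intervention arm has fewer zeros, for example through more follow-up contact.

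Finally, the SAP is not at hand and may set a rule for zeros. All of this stands as a limit on size and certainty. It does not remove the point, because the protocol does not leave the model open: it names a distribution that the outcome probably does not follow. The optional non-parametric tests are no remedy, since they do not estimate the percent change in mean cost that is to be reported.

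**Conclusion.** The point holds in a limited form. The gamma model is carried over from a cost that is always positive to one that can be zero, with no provision for zeros, so the result could depend on a software default or a choice made after the data are seen. If zeros are dropped and readmissions are prevented, the ratio of means moves from 0.30 to about 1.0 at the bound and from 0.34 to 0.47 in the 25% case; with 75% of non-readmitted patients having some cost, it hardly moves (0.40 to 0.42). These figures rest on the protocol's 23% and odds ratio of 0.25, equal mean cost per readmission in both arms, and an assumed small cost of 5% of a readmission.

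The power statement cannot be judged until the basis of 2.8 is known: about 85% if zeros were included, and 66% or 46% in the two illustrations if they were not. This concerns one secondary endpoint. The primary hospitalization cost is not affected by zeros. The change should be made before the data are seen.

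**What to change.** State in section 6.1 that cost from discharge to 30 days is analysed in all randomised patients, with zero costs included. Estimate the ratio of means with a log-link quasi-likelihood model (treatment and site as fixed effects) and robust standard errors. A two-part model is an alternative if it reports the overall ratio of means with a bootstrap interval, and not only the ratio among patients with positive cost.

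In the Power analysis, give the share of zero-cost patients in the preliminary data and say whether 2.8 was computed with them. If it was, the power claim can stand as conservative. If not, recompute it from the all-patient variance.

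The analysis change costs a sentence of protocol text and a few lines of code, and the exponentiated coefficient keeps its meaning as the ratio of means. The possible cost is in the power claim: if 2.8 came from positive costs only, the restated figure may be clearly below 80%.

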### **2.2 Secondary Aims**

1. Demonstrate rural home hospital care improves days at home, physical activity, and readmission.

- For example: reduced length of stay, increased daily steps and hours of physical activity per day.

2. Synthesize lessons learned to prepare a dissemination guide for a future multi-site implementation.

- For example: clinical and administrative data including data collected from the process measures and qualitative interviews with patients and caregivers.
- Clinician process measures survey with rural home hospital clinicians
- Qualitative interviews with rural home hospital clinicians.

Please refer to our performance measures below for more details regarding the definitions and sources for each of these measures

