### ***Power analysis***

A priori (based on data from our previous randomized controlled trial of urban home hospital care), we expect the mean cost to be mean cost on intervention to be 40% lower than in control (leading to a ratio of mean costs in treatment to control to be at most .6). Thus, for our power calculation, we want to be able to detect that the exponential of the treatment effect in our

gamma regression to be 0.6 or lower., We will require 132 patients total (66 in each arm, and 44 total per site) to detect a 40% relative decrease in mean direct cost in home versus hospital (power: 80%, alpha: 0.05, two-tailed) using the Wald test for the treatment effect from a gamma regression model for costs discussed above. In this power calculation, we assume the over-dispersion parameter for the gamma distribution variance is 1.2 (as seen from our preliminary data). Although we hope to recruit 75 patients in each arm, 66 patients will give us more than adequate power (80%) to detect the clinically expected difference.

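### The 80% power stated for 30-day readmission does not follow from its own inputs: they give about 45–50% at the stated 1% level and about 69–77% at 5%

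*Protocol*

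**What the plan says.** Protocol section 6.1, under Power analysis, plans the secondary outcomes at 80% power, "with Type 1 error of 1%, approximately the type 1 error when using the Benjamini-Hochberg method as noted above". For readmission it names the model, "For percent with 30-day readmission, using logistic regression model with treatment and site effects", and then claims that "with 66 patients in each arm, we have 80% to detect on odds ratio of 0.25 for intervention on control". The control rate behind this claim is given in brackets as a planning input: "assuming the percent 30 day readmission in controls is 23% as seen in preliminary data".

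The sample size itself comes from the primary cost outcome: "132 patients total (66 in each arm, and 44 total per site", with "power: 80%, alpha: 0.05, two-tailed". The sponsor adds: "Although we hope to recruit 75 patients in each arm". No one-sided test is mentioned anywhere.

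Section 6.1 also gives the rule for declaring secondary results: Benjamini-Hochberg across the secondary outcomes with a false discovery rate of 0.2. Section 5.5.2 lists four such endpoints: cost from discharge to 30 days, unplanned 30-day readmission, days at home, and percent of day lying down. Readmission is also part of a named aim in section 2.2: "Demonstrate rural home hospital care improves days at home, physical activity, and readmission".

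**The concern.** All the inputs for the readmission power are printed (number per arm, odds ratio, control rate, level and model), so the figure can be checked without a separate analysis plan. Only about 20 events are expected in total, which is few for 80% power at a 1% level.

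What is at stake is how a null result is read. Section 1.1.2 says that a null result would still be informative. A reader told that power was 80% would take a non-significant readmission result as fairly strong evidence against a four-fold reduction in odds. With lower true power it is weaker evidence than that.

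**Working it through.** **Inputs** (Protocol, section 6.1, Power analysis): n = 66 per arm; control rate p1 = 0.23; odds ratio 0.25; alpha = 0.01. Two-sided testing is stated for the primary outcome and assumed here for readmission. No dropout is stated and none is applied.

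**Home-arm rate.** Control odds = 0.23/0.77 = 0.2987. Times 0.25 = 0.0747. p2 = 0.0747/1.0747 = 0.0695. Expected events: 66 × 0.23 = 15.2 and 66 × 0.0695 = 4.6.

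**Wald formula for the log odds ratio.**
- SE = sqrt[1/(66 × 0.23 × 0.77) + 1/(66 × 0.0695 × 0.9305)] = sqrt(0.0856 + 0.2343) = 0.566
- |ln 0.25|/SE = 1.386/0.566 = 2.451
- Power at 1%: Φ(2.451 − 2.576) = 0.450
- Power at 5%: Φ(2.451 − 1.960) = 0.688

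**Pooled two-proportion formula.**
- Difference = 0.1605; mean rate = 0.1497
- SE under the null = sqrt(2 × 0.1497 × 0.8503/66) = 0.0621
- SE under the alternative = sqrt[(0.1771 + 0.0647)/66] = 0.0605
- Power at 1%: Φ[(0.1605 − 2.576 × 0.0621)/0.0605] = 0.503
- Power at 5%: Φ[(0.1605 − 1.960 × 0.0621)/0.0605] = 0.739

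**Checks without the normal approximation to power.** The table gives exact binomial enumeration, and 6,000 simulated logistic regressions with treatment and three equal sites, assuming no site effect.

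| Method, 66 per arm, two-sided | 1% | 5% |
|---|---|---|
| Wald formula | 45.0% | 68.8% |
| Pooled formula | 50.3% | 73.9% |
| Exact, Wald | 42.0% | 73.8% |
| Exact, chi-square | 51.6% | 75.5% |
| Exact, likelihood ratio | 54.0% | 77.0% |
| Simulated logistic with site, Wald | 43.9% | 73.7% |
| Simulated logistic with site, likelihood ratio | 55.7% | 77.5% |

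**Trying to recover the stated 80%.** Four routes come close, and each departs from something the protocol states.
- A null-variance logistic formula at the mean event rate gives 81.1% at 5%, but 60.5% at 1%.
- The same formula with 23% in both arms gives 78.1% at 1%, but 23% is the control rate and the home arm would be at 7%.
- Reading 0.25 as a relative risk gives 81.4% at 5%, but 60.1% at 1%.
- A one-sided 5% test gives 79.0% (Wald) to 83.2% (pooled).

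**What 80% would take.** For an odds ratio of 0.25: 114 (pooled) or 129 (Wald) per arm at 1%, and 77 or 87 per arm at 5%. With 66 per arm, the pooled formula reaches 80% at an odds ratio of about 0.11 at 1% (power 79.9%) and about 0.21 at 5% (power 80.5%).

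**Level under the planned rule.** With four endpoints and a false discovery rate of 0.2, the Benjamini-Hochberg steps are 0.2 × k/4 = 0.05, 0.10, 0.15 and 0.20. A p-value of 0.05 or less meets the step at whatever rank it holds, so it is always rejected. A first step of 1% would need 0.2/0.01 = 20 outcomes.

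**The case against.** The strongest reply is that 1% is not the rule by which readmission will be judged. The protocol calls it an approximation to Benjamini-Hochberg, and with four endpoints the strictest step is 5%. Power under the planned analysis is therefore at least the 5% figure. It is higher if other secondary outcomes also succeed: at a two-sided 10% level the Wald and pooled formulas give 79% and 83%. This stands. A reader might infer from the 1% figures that the trial would miss a four-fold reduction in odds about half the time. The documents do not support that; under the planned rule the miss rate is at most about a quarter to a third.

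The gap at 5% is also modest and depends partly on the method: about 11 points by the Wald formula, but 3–6 by exact enumeration of the Wald, chi-square and likelihood-ratio tests. At the hoped-for 75 per arm, 5% power is 74–79% by the two formulas and 79–81% by the same exact tests, so the claim would then be roughly met. These points stand too, but the protocol attaches its 80% to 66 per arm and a 1% level, and the figure printed there is wrong.

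It is also tempting to say that no two-sided calculation yields 80%. That goes too far, because the null-variance formula at the mean rate is a recognised planning approximation and gives 81% at 5%. It does not match exact power at these inputs, and it uses a level other than the one stated.

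Finally, one might want the protocol to replace a Wald test because the home arm expects few events. The protocol names a Wald test only for the primary gamma model. For readmission it says logistic regression and no more, and the choice of test can properly be left to the analysis plan.

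**Conclusion.** The point holds as an error in a stated figure. With 66 per arm, 23% versus 6.95% and two-sided testing, power at the stated 1% level is about 45–50% by the standard formulas and 42–54% by exact enumeration, against a claimed 80%: an overstatement of about 25–38 points. At 5% power is about 69–77%, an overstatement of about 3–11 points.

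The 5% figure is the floor for the planned analysis, provided that the Benjamini-Hochberg family is the four endpoints of section 5.5.2. The result also assumes no loss to follow-up, since none is stated, and the simulation assumes no site effect. Where the 80% came from cannot be settled from the document.

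The trial's size is set by the primary cost outcome and is not affected. The finding does not show that the trial is too small for its primary purpose. It shows only that the readmission power should not be quoted as 80% at 1%.

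**What to change.** Replace the readmission sentence in section 6.1 with one calculated by a single named method, for example:

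> With 66 per arm and 23% readmission in controls, two-sided power for an odds ratio of 0.25 is about 50% at 1% and 74% at 5% (pooled two-proportion formula); 80% power corresponds to odds ratios of about 0.11 and 0.21.

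State next to it which level matches the Benjamini-Hochberg rule. With four secondary endpoints and a false discovery rate of 0.2, the first step is 5%, not 1%. Powers and detectable odds ratios should come from the same method, because formula and exact values differ by enough to create a new inconsistency.

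The cost is a text change. No patients are added and no analysis or test changes. The printed power becomes less favourable.

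### The power claim for days at home rests on a rise from 29 to 48 days in a window of 30 (or 31) days, and the protocol names three different models for this endpoint

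*Protocol*

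**What the plan says.** - **Endpoint.** Protocol section 5.5.2 lists days at home as one of four secondary endpoints and defines it as "the number of days spent at home from the day of discharge to 30-days later".
- **Power.** Section 6.1, Power analysis, claims over 80% power with 66 patients per arm for an "expected 65% increase in the number days at home for control to intervention (from 29 days to 48, days". The type I error for secondary outcomes is put at 1%. No sidedness is given there; the primary outcome is tested two-tailed.
- **Model behind the power.** The sentence begins "For the number of days at home, using a log-normal distribution with treatment and site effects" and ends by "assuming the over-dispersion parameter for the negative binomial distribution is 1.4".
- **Analysis model.** The Quantitative part of section 6.1 assigns "negative binomial regression for count outcomes such as days at home, and non-transformed linear regression for normally distributed continuous outcomes (e.g., days at home"), qualified by a proviso that each is used where it fits.
- **Lying down.** In the same paragraph of the power analysis, time lying down is powered "using a negative binomial regression model with a logistic link", also with a dispersion of 1.4.

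**The concern.** The alternative used for the power lies outside the range of the endpoint. It is not a stray digit: the 65% and the 48 days agree with each other, so the whole calculation was run on an effect that no trial could observe. The dispersion does not fit the window either.

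Days at home also appears as the example for a count model and for a normal-errors model in one sentence, and is then powered under a log-normal model that takes a negative binomial dispersion. These are three different analyses, and the protocol does not settle which applies.

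Days at home is the first outcome named in Secondary Aim 1 (section 2.2). A reader who trusts the stated power would take a null result as good evidence of no effect. With the model left open, the choice could also be made after the data are seen.

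**Working it through.** **Inputs (protocol).** Window 30 days, or 31 if both end days count (5.5.2). Means 29 and 48, increase 65%, dispersion 1.4, 66 per arm, type I error 1%, power over 80% (6.1, Power analysis). Two-sided testing is assumed, as for the primary outcome.

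**1. Is 48 intended?** 29 × 1.65 = 47.85, which rounds to 48. It exceeds the ceiling by 18 days (17 for a 31-day count).

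**2. Largest possible effect from 29.** 30/29 = 1.034, a gain of 1 day or 3.4%. 31/29 = 1.069, a gain of 2 days or 6.9%. Either needs every intervention patient to be at home on every day.

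**3. Is the dispersion possible?** A negative binomial with variance μ + 1.4μ² has, at μ = 29, an SD of √(29 + 1.4 × 841) = 34.7 days. A variable confined to 0–30 with mean 29 has an SD of at most √(29 × 1) = 5.4; on 0–31 the limit is √(29 × 2) = 7.6. If 1.4 is instead the size parameter (variance μ + μ²/1.4), the SD is √(29 + 600.7) = 25.1, still far outside.

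**4. Does the stated power follow, even for the 65% increase?** Power = Φ( ln 1.65 / √[(v₁ + v₂)/66] − 2.576 ), with ln 1.65 = 0.501. For the negative binomial with dispersion 1.4, v₁ = 1/29 + 1.4 = 1.434 and v₂ = 1/48 + 1.4 = 1.421. The standard error is √(2.855/66) = 0.208 and power = Φ(2.408 − 2.576) = 43%. The protocol does not say how 1.4 is parameterised, so other readings were tried:

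| Reading of 1.4 | Power, two-sided 1% |
|---|---|
| Log-normal, SD of the log | 30% |
| Negative binomial dispersion | 43% |
| Log-normal, variance of the log | 44% |
| Log-normal, CV | 57% |
| Log-normal, CV² | 69% |
| Negative binomial size | 78% |

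More than 80% appears only under readings that the text does not give:
- quasi-Poisson variance: about 100%
- log-normal with CV² = 1/1.4: 91%
- the size reading tested one-sided at 1%: 84.5%
- two-sided 5% with CV² = 1.4: 87%
- two-sided 5% with the size reading: 92%

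**5. What could be detected within the window?** No SD is given, so the values here are assumptions. For a difference d in means with equal SDs, power at two-sided 1% is Φ( d / (SD × √(2/66)) − 2.576 ), with √(2/66) = 0.174.

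| Assumed SD (days) | d = 1 day | d = 2 days (31-day count only) |
|---|---|---|
| 2 | 62% | 99.9% |
| 3 | 25% | 90% |
| 4 | 13% | 62% |
| 5 | 8% | 39% |

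Equal SDs are a simplification: an arm whose mean sits at the ceiling has an SD of zero.

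**6. Detectable difference at 80% power, 66 per arm.** At two-sided 1%: (2.576 + 0.842) × 0.174 = 0.60 × SD. At two-sided 5%: (1.960 + 0.842) × 0.174 = 0.49 × SD.

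**7. Lying down, for comparison.** With dispersion 1.4, a 65% reduction (ratio 0.35) and two-sided 1%, the method of step 4 gives 97% to 99% for assumed control means of 5 to 20 hours. The stated figure of over 90% is reproduced.

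**The case against.** The strongest defence is that little depends on this figure. The total of 132 comes from the primary cost outcome, days at home is one of four secondary endpoints, and section 6.1 leaves room for the model that fits and for non-parametric tests. A statistical analysis plan that is not shown may name the final model. This limits the consequence and it stands. It does not rescue a stated power computed for an unattainable mean. Nor does it explain how one endpoint can be the example for two kinds of model, with a third used for its power.

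Some stronger readings are tempting, but the document does not support them:

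- **A reader might infer that the trial has essentially no power for this endpoint.** Putting 30/29 or 31/29 into the negative binomial formula with dispersion 1.4 gives 0.8% or 1.2%. That uses the very variance that step 3 shows to be impossible. With SDs that the window allows, power ranges widely.
- **A reader might take 43% or 44% as the correct power for 48 days.** Those figures depend on one parameterisation of 1.4, which the protocol leaves undefined.
- **A reader might infer that a fitted negative binomial would give impossible standard errors.** The 1.4 is a planning value; a fitted model estimates its own dispersion.
- **A reader might infer that the control mean of 29 is wrong.** It is attainable. The pairing of 29 with 48 is not.
- **A reader might extend the fault to lying down.** A 65% reduction is possible within 24 hours, and the stated power reproduces. Only the link wording is plainly wrong there.

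**Conclusion.** The concern holds for days at home. The claim of over 80% power is unsupported, because the assumed intervention mean exceeds the endpoint's maximum by 17 to 18 days and the negative binomial dispersion of 1.4 cannot occur in this window. Neither result depends on whether the window is counted as 30 or 31 days. Even with the unattainable effect granted, the plain readings of the stated inputs give about 30% to 78% at two-sided 1%.

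The actual power cannot be computed from the protocol. For a one-day difference at 1% it would be 62%, 25%, 13% or 8% at assumed SDs of 2, 3, 4 or 5 days, equal in both arms. The conflict between negative binomial, untransformed linear and log-normal models is a separate defect of wording that needs settling. Both defects are confined to this secondary endpoint.

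**What to change.** - **Power statement (section 6.1, Power analysis).** Delete the 65% claim with its 29 and 48 days. Alternatively, replace it with a detectable difference in days that fits the window: 0.60 × SD at 1% or 0.49 × SD at 5% with 66 per arm, taking the SD from the preliminary data. Set that difference beside the room left above the control mean, which is 1 to 2 days if 29 is kept.
- **Model (section 6.1, both places).** Name one model suited to a bounded outcome and use it for analysis and power alike. One example is a difference in mean days by linear regression with robust standard errors, adjusted for site.
- **Window (section 5.5.2).** State whether the maximum is 30 or 31 days.
- **Minor and separate.** Correct the link named for the negative binomial model of time lying down. Its stated power is not shown to be wrong.

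The cost is a change of wording, one recalculation and a less favourable stated power for one secondary endpoint. No extra patients are needed.
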